## Abstract

**Background:**

Ghana introduced what has come to be known as the 'Free’ Maternal Health Care Policy (FMHCP) in 2008 via the free registration of pregnant women to the National Health Insurance Scheme to access healthcare free of charge. The policy targeted every pregnant woman in Ghana with a full benefits package covering comprehensive maternal healthcare.

**Purpose:**

This study seeks to measure the contribution of the FMHCP to maternal healthcare utilization; antenatal care uptake, and facility delivery and determine the utilization impact on stillbirth, perinatal, and neonatal deaths using quasi-experimental methods. The study will also contextualize the findings against funding constraints and operational bottlenecks surrounding the policy operations in the Upper East Region of Ghana.

**Methods:**

This study adopts a mixed-method design to estimate the treatment effect using variables generated from historical data of Ghana and Kenya Demographic and Health Survey data sets of 2008/2014, as treatment and comparison groups respectively. As DHS uses complex design, weighting will be applied to the data sets to cater for clustering and stratification at all stages of the analysis by setting the data in STATA and prefix Stata commands with *‘svy’*. Thus, the policy impact will be determined using quasi-experimental designs; propensity score matching, and difference-in-differences methods. Prevalence, mean difference, and test of association between outcome and exposure variables will be achieved using the Rao Scot Chi-square. Confounding variables will be adjusted for using Poisson and multiple logistics regression models. Statistical results will be reported in proportions, regression coefficient, and risk ratios. This study then employs intrinsic-case study technique to explore the current operations of the ‘free’ policy in Ghana, using qualitative methods to obtain primary data from the Upper East Region of Ghana for an in-depth analysis.

**Discussion:**

The study discussions will show the contributions of the ‘free’ policy towards maternal healthcare utilization and its performance towards stillbirth, perinatal and neonatal healthcare outcomes. The discussions will also centre on policy designs and implementation in resource constraints settings showing how SDG3 can be achievement or otherwise. Effectiveness of policy proxy and gains in the context of social health insurance within a broader concept of population health and economic burden will also be conferred.

**Protocol approval:**

This study protocol is registered for implementation by the Ghana Health Service Ethical Review Committee, number: GHS-ERC 002/04/19.

## Plain language summary

In July 2008, Ghana introduced what is termed the Free Maternal Health Care Policy across the country through the free registration of all pregnant women to its National Health Insurance Scheme (NHIS). The policy objective was to eliminate the financial barrier to access thereby increasing antenatal care up-take and facility delivery utilization among pregnant women and postnatal care service for nursing mothers with their newborn babies, free of charge up to 90 days.

The objective of this current study is to determine the magnitude of utilization the policy chalked since its inception and to measure its effect on newborn care outcomes in Ghana. The study also wants to examine the policy used in its current state, against the background of delayed claims payments by the national health insurance scheme to service providers.

This research is in two parts: first, using existing data from Ghana and Kenya, and comparing between the two countries; Ghana as the group that received the ‘free’ policy and Kenya as the group that did not receive the policy at the time. The second part of the study will collect information from doctors, midwives, hospital administrators and pregnant women in the Upper East Region of Ghana, one of the regions with a high subscription to the ‘free’ policy and also examined available records in the hospitals, to understand and explain the policy current state and how that clarifies the results from the existing data.

This study is expected to contribute to knowledge in the area of the policy implications for newborn care in Ghana. Policy gaps will be thoroughly discussed, as it pertains to scarce resource and funding difficulties in developing countries in Sub-Saharan Africa. The study will measure in-country strides i.e. Ghana’s feat towards the attainment of Sustainable Development Goal 3 and make projections and predictions on Ghana’s chance of realizing the 12 per 1000 live births rate set for countries by the World Health Organization (WHO) to be achieved by the year 2030.

The study will offer rich literature to research and policy in the area of newborn care and outcomes, a rather understudied concept, in Ghana and Sub-Saharan Africa.

## Background

Despite the modest gains from maternal and child healthcare interventions across the world, reproductive health issues remain a global challenge, particularly in developing countries. It is estimated globally that, more than 300,000 women died out of pregnancy or childbearing related conditions in 2015, with about 3 million neonatal deaths and 2.6 million stillbirths [1–4].

Among these figures exist a sharp disparity between and within countries. For example, stillbirth rates in Japan reduced from 18 per 1000 live births to 3 per 1000 live births between 1979 and 2010. In the United Kingdom, it was estimated that 1 in 200 pregnancies end in stillbirth [5–7].

Conversely, Nigeria alone, Africa’s most populous country recorded 42 per 1000 live births in 2015, which translated to over 300,000 babies dying before they are born [20, 21]. Albeit Ghana compares better to Nigeria, 28 per 1000 live births were also reported about the same period [8, 9]. In general, more than 98% of the world stillbirth estimates are accounted for by developing countries, particularly Sub-Saharan Africa and South Asia [10–13].

Recent studies have shown that quality antenatal care, during which time screenings are carried out on pregnant mothers to pick high-risk ones for target monitoring and management, can improve pregnancy outcomes and also minimize the risk of maternal morbidity and mortality [3, 14–16]. This principle holds for skilled delivery as well, often at a healthcare facility, where high-risk mothers and babies are managed using structured programs of emergency obstetric and neonatal intensive care [17, 18].

Nonetheless, country level and household income disparities exist widely across regions and have rather restricted access to maternal healthcare to the privileged, thereby stretching the inequality margin. Consequently, political leaders have introduced pro-poor policies as the panacea to bridging the access gap relative to maternal and child healthcare [19–22].

Within country policy interventions have ranged from equitable access to healthcare to the provision of quality healthcare at all levels for pregnant mothers and newborns [22–24]. In a similar vein, Ghana introduced one of such policies in 2008 dubbed, the ‘Free’ Maternal Healthcare Policy (FMHCP) with a primary aim of increasing facility delivery utilization and to achieve maternal and newborn care in general [3, 25, 26].

Essentially, the ‘free’ policy lacked an operational framework for implementation, but had a political directive that ensured that every pregnant woman gets to register with the national health insurance scheme (NHIS), without paying a premium, and then access comprehensive maternal healthcare free of charge from NHIS accredited health service providers up to 90 days post-delivery [25, 27].

The government of Ghana has since invested several millions of Ghana cedis in a bid to keep the policy running amidst NHIS reimbursement challenges. With nearly 3million women benefitting from the ‘free’ package as by 2013 [28, 29], studies are yet to report on the policy gains or otherwise relative to perinatal healthcare outcome.

Despite the huge financial investment on the free policy intervention, literature is rather restricted to reporting on a nominal increase in attendance at healthcare facilities regardless of time-variant factors and somewhat monotonously on factors that affect the implementation process. Moreover, the existing literature turns to focus more on the policy effects on mothers and less on the unborn and the newborn.

Thus far, the ‘free’ maternal health care policy relationship with maternal healthcare utilization and outcomes, vis a vis medium to long term impact on perinatal healthcare has yet to be adequately documented [30–32].

Incidentally, perinatal death is also poorly researched in Ghana and Sub-Saharan Africa despite its economic burdening abilities [11, 14]. Stillbirth which accounts for a large portion of perinatal deaths has been estimated to have dire consequences on household healthcare expenditure, particularly in areas where the ratios are considered worse than child mortality due to malaria and HIV/AIDS [33–35].

This notwithstanding, perinatal deaths continue to receive little attention in public health and policy research [36, 37]. Hence, this current study seeks to examine the ‘free’ policy effect on maternal healthcare utilization after a decade of implementation and to measures its contributions towards the reduction of stillbirth, perinatal deaths, and neonatal mortality in Ghana.

## Overall study goal

To evaluate the contribution of the ‘free’ maternal health care policy towards maternal healthcare utilization and measure its impact on perinatal healthcare outcomes in Ghana.

## Specific objectives

To determine any significance in association between the FMHCP and antenatal care uptake, and facility delivery utilization in Ghana.To compare the difference in perinatal outcomes between Ghana and Kenya relative to the ‘free’ maternal health care policy.To measure the treatment effect of facility delivery on stillbirth, perinatal deaths, and neonatal mortality among women who received the FMHCP program compared to those who did not receive the program.To describe the ‘free’ maternal health care policy implementation in its current state in Ghana, within the context of funding constraints and implementation bottlenecks.

## Research questions

The study will address the following research questionsWhat is the relationship between antenatal care, facility delivery utilization, and the free maternal health care policy?What is the treatment effect of facility delivery utilization on stillbirth among women who received the ‘free’ maternal health care policy?What is the treatment difference of facility delivery utilization on perinatal and neonatal mortalities among women who received the ‘free’ policy treatment, compared with those who did not receive the policy?How free is the ‘free’ maternal health care policy relative to implementation, against the background of delays in claims paid by the NHIS in Ghana?

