## Hypothesis

This study hypothesis that;H_0_:There is no significant association between antenatal care uptake and the free maternal health care policy.H_0_:There is no significant association between facility delivery utilization and perinatal deaths among women who received the free maternal healthcare policy.H_0_**:**Facility delivery utilization has no significant treatment effect on perinatal deaths among women who received the free maternal health care policy.

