## Operational definitions

*Utilization*: The use of maternal healthcare services rendered in a healthcare facility at any level.

*Maternal healthcare*: Antenatal care clinics and facility delivery services provided to pregnant women in a healthcare facility.

*Antenatal care uptake*: This refers to a 4+ antenatal care visit, thus, antenatal clinic visits of less than 4 are equal to zero visits (or 'no visit').

*Facility delivery*: This is when a pregnant woman gives birth in a healthcare facility at any level.

*Stillbirth*: This refers to the birth of a fetus with no signs of life, after 28 weeks of gestation or the death of a fetus within 24 h after birth.

*Perinatal death*: This refers to the number of stillbirth plus the death of neonates within the first week of life.

*Neonatal deaths*: This refers to the number of newborn deaths within 28 days of life.

*Treatment group*: Pregnant women study participants registered with the national health insurance scheme and made 4+ antenatal care visits or pregnant women participants in Ghana who delivered in a healthcare facility.

*Comparison group*: Pregnant women study participants registered with the national health insurance but have made less than 4 antenatal care visits with less than four minimum antenatal visits or pregnant women who did not deliver in a healthcare facility within the study period.

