### Variables of interest

The maternal healthcare utilization examines two primary outcome variables which include; antenatal care up-take (4+ visit = 1, and ≤ 3 visits = 0), and facility delivery utilization, also binary outcome (facility delivery = 1 and home delivery = 0). Mothers’ health insurance status (proxy to the FMHCP) is the exposure variable of interest in this study.

Stillbirth, perinatal death, and neonatal mortality are secondary outcome variables of interest generated as binary outcomes from the DHS data sets using variable *b6,* and *b7* against which the policy utilization impact will be measured. Table 5 presents the derived variables generated using STATA 15.0 from the 2008/2014 DHS data sets.

**Table 5 Tab5:** Variables of interest

Item	Label	Name	Recoding	Binary V
1	Respondent holds valid NHIS card	*S1015*	Holds a valid NHIS card (with or with no evidence) = 1 No valid NHIS card = 0	*Vid_1*
2	Respondent hold valid NHIS card	*S1015*	Holds a valid NHIS card (with evidence) = 1 No valid NHIS card plus (holds a valid NHIS card with no evidence) = 0	*Vid_2*
3	Number of ANC visit during pregnancy	*m14*	Antenatal visits 0–3 = 0 Antenatal visits ≥ 4 = 1	*anc4*
4		*m15*	Home delivery = 0 All facility delivery = 1	*fdelivery*
5	Age at death	*b6*	Alive after day 0 = 0 Born dead/died on day 0 = 1	*stillbirth*
6	Age at death	*b6*	Did not die before 7th day = 0 Died before 7th day of life = 1	*prdeaths*
7	Age at death (months imputed)	*b7*	Did not die before 28th day = 0 Died before 28th day of life = 1	*neodeaths*

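### The plan seeks a treatment effect of facility delivery on stillbirth and perinatal death, but as defined these outcomes include fetuses that died before the exposure could act

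*Protocol article*

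**What the plan says.** - **Question and hypothesis.** Under Research questions, the second question is "What is the treatment effect of facility delivery utilization on stillbirth among women who received" the policy. Specific objective 3 is "To measure the treatment effect of facility delivery on stillbirth, perinatal deaths, and neonatal mortality". The third null hypothesis is "Facility delivery utilization has no significant treatment effect on perinatal deaths among women who received the free maternal health care policy". The third research question asks for a treatment difference by facility delivery in perinatal and neonatal mortality. The second null hypothesis speaks only of an association between facility delivery and perinatal deaths.
- **Exposure.** Operational definitions, facility delivery: "This is when a pregnant woman gives birth in a healthcare facility at any level".
- **Outcomes.** Operational definitions, stillbirth: "This refers to the birth of a fetus with no signs of life, after 28 weeks of gestation", to which deaths in the 24 hours after birth are added. Perinatal death: "This refers to the number of stillbirth plus the death of neonates within the first week of life".
- **Coding.** Table 5 derives the stillbirth variable from b6, labelled as age at death, with "Born dead/died on day 0 = 1". The perinatal variable also comes from b6 and counts deaths before day 7, without naming stillbirths. Data source and size says that the children's files are used.
- **Method.** Study design and Statistical assumptions rest the matching on there being no systematic unobserved differences. The adjustment lists under Covariates and Data analysis hold maternal, pregnancy and population characteristics. None records whether the fetus was alive when labour began.

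**The concern.** An effect of place of delivery can act only from labour onwards. The stillbirth definition does not separate deaths before labour from deaths during it, and no restriction to fetuses alive at the onset of labour is stated. For deaths before labour the order is reversed: the outcome comes first, and a known fetal death may itself influence where the woman delivers. This differs from ordinary confounding by maternal characteristics, so adding maternal covariates does not solve it.

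At stake is the reading of the second research question, objective 3 and the third hypothesis. Deaths before labour can dilute a real benefit, hide it, turn it into apparent harm or exaggerate it, depending on where those births take place. The protocol intends to draw policy conclusions from these results.

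**Working it through.** **1. Time order.** Setting the definitions side by side:

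| Component of the outcome | Can it follow place of delivery? |
|---|---|
| Fetal death before labour | No |
| Fetal death during labour | Yes |
| Death within 24 hours of a live birth | Yes |
| Death later in the first week | Yes |

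Stillbirth as defined holds the first three rows, perinatal death all four. Neonatal death lacks the first two.

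**2. Possible size for stillbirth.** The plan gives no figure to reproduce here. All four inputs are assumptions, because the document states none of them:

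- a = share of all deaths counted as stillbirths that occur before labour: 0.30, 0.45, 0.60
- f = share of other births that take place in facilities: 0.57
- p = share of deaths before labour that are delivered in facilities: 0.45, 0.57, 0.65, 0.70
- R = true risk ratio, facility against home, for the remaining deaths: 0.70, or 1.00 for no effect

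Of the remaining deaths, the share in facilities is q = fR / (fR + 1 − f). With R = 0.70, q = 0.399 / 0.829 = 0.481. With R = 1.00, q = 0.57.

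The facility share of all stillbirths is S = a·p + (1 − a)·q, and the observed RR = (S / 0.57) / ((1 − S) / 0.43).

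Examples with R = 0.70:
- a = 0.30, p = 0.57: S = 0.171 + 0.337 = 0.508, so RR = 0.891 / 1.144 = 0.78.
- a = 0.60, p = 0.70: S = 0.420 + 0.193 = 0.613, so RR = 1.075 / 0.901 = 1.19.

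| p | R = 0.70: a = 0.30 / 0.45 / 0.60 | R = 1.00: a = 0.30 / 0.45 / 0.60 |
|---|---|---|
| 0.45 | 0.67 / 0.66 / 0.65 | 0.86 / 0.80 / 0.75 |
| 0.57 | 0.78 / 0.82 / 0.87 | 1.00 / 1.00 / 1.00 |
| 0.65 | 0.86 / 0.95 / 1.05 | 1.10 / 1.16 / 1.22 |
| 0.70 | 0.91 / 1.04 / 1.19 | 1.18 / 1.28 / 1.39 |

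With R = 0.70, three of the six cells at p = 0.65 or 0.70 lie above 1.

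**3. Point of reversal.** Setting S = f gives p = (f − (1 − a)·q) / a. With R = 0.70 this is 0.78, 0.68 and 0.63 for a = 0.30, 0.45 and 0.60.

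**4. Check with full denominators.** The formula in step 2 keeps births in the ratio 57:43. Take the Background rate for Ghana, 28 per 1000, and count deaths before labour in the denominators, for a = 0.60, p = 0.70, R = 0.70. Facility births are 0.9832 × 0.57 + 0.0168 × 0.70 = 0.5722, with 0.028 × 0.6125 = 0.01715 stillbirths, or 30.0 per 1000. Home births are 0.4278, with 0.028 × 0.3875 = 0.01085, or 25.4 per 1000. The ratio is 1.18 against 1.19, so the approximation is adequate.

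A separate calculation with full denominators (f = 0.60, a = 0.50, R = 0.70) gave 0.57, 0.84, 1.02 and 1.26 for p = 0.4, 0.6, 0.7 and 0.8. The pattern is the same.

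**The case against.** **The coded outcome may contain no such deaths.** This is the strongest objection. The outcomes come from children's files through an age-at-death variable, and the perinatal code does not mention stillbirths. If b6 holds no births without signs of life, no death before labour enters, and the bias in the coded variables is zero. This stands as a limit on the practical effect. It does not rescue the question as defined: the variable would then be day-0 death among live births and could not be reported as stillbirth.

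**The direction is not fixed.** This also stands. A reader might infer that the analysis will show facilities as harmful. The document gives no share of deaths before labour and no place of delivery for them, so it supports neither direction, and the 45% row shows exaggerated benefit.

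**Not every statement claims an effect.** A reader might count the second null hypothesis among the treatment-effect claims. It claims an association only, although it uses the same mixed outcome.

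**Part of perinatal death can follow the exposure.** This is correct. A reader might conclude that no effect on perinatal death is estimable at all, which goes too far: deaths during labour and in the first week can follow place of delivery. The figures above are for stillbirth and do not carry over unchanged to perinatal death.

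**Restricting to live births has its own bias.** This is true, and the fix must say so.

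**Conclusion.** The point holds for the second research question, objective 3, the third null hypothesis and the perinatal part of the third research question. As defined, part of the outcome precedes the exposure, and neither the planned matching nor the planned regression can correct that.

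Under the stated assumptions a true risk ratio of 0.70 appears as 0.78-0.87 when place of delivery is unrelated to prior fetal death. It appears as 0.86-1.19 when 65-70% of such deaths are delivered in facilities, and as 0.65-0.67 when 45% are. With no true effect, the 65-70% case gives 1.10-1.39. These ranges show what could happen and do not predict the result. They apply to the coded variables only if b6 includes births without signs of life.

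Neonatal mortality, the two primary outcomes and the Ghana-Kenya policy comparison are not affected. Since the affected outcomes are secondary, this is a change that should be made, but it does not undermine the study as a whole.

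**What to change.** 1. Establish and state whether b6 includes births without signs of life. If it does not, rename the Table 5 stillbirth variable as day-0 death among live births, and do not report it as stillbirth.
2. Report no treatment effect of place of delivery on stillbirth or on the stillbirth part of perinatal death. Describe any such result as an association.
3. Estimate the facility-delivery effect on deaths at days 0-6 and days 0-27 among live births.
4. Reword the second research question, the perinatal part of the third, objective 3 and the third null hypothesis to match.
5. Relate stillbirth to the policy only if the data identify stillbirths.

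The cost is a check of one variable, an outcome restriction and rewording; the data are secondary, so no new collection is needed. Two downsides should be stated in the protocol. Any effect of facility delivery on deaths during labour is no longer estimated. Restricting to live births also selects on an event after the exposure begins: if facility care turns deaths in labour into live births that die early, facilities will look worse than they are.

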## Hypothesis

This study hypothesis that;H_0_:There is no significant association between antenatal care uptake and the free maternal health care policy.H_0_:There is no significant association between facility delivery utilization and perinatal deaths among women who received the free maternal healthcare policy.H_0_**:**Facility delivery utilization has no significant treatment effect on perinatal deaths among women who received the free maternal health care policy.

